**Fig. 2 Fig2:**
[figure not shown]
Algorithm for defining repeat infection. PCR = polymerase chain reaction, WGS = whole genome sequencing, mRNA = messenger ribonucleic acid

### Follow up

Men will be required to provide specimens and behavioral data until the conclusion of the trial at 4 weeks (Table 1). Men will be asked to attend the clinic at 4 weeks for a final study visit. At the 4-week visit, the research nurse will administer a final paper questionnaire and additional rectal swabs will be self-collected for WGS and mRNA assay.

**Table 1 Tab1:** Trial timeline

		Recruitment Day 1	Days 2-6	Day 7	Day 14	Day 21	Follow up Day 28
Recruitment							
Pre-eligibility assessment		X					
Informed consent obtained		X					
Enrollment and randomisation		X					
Dosage under supervision		X					
Data collection	Format						
Baseline questionnaire	Paper	X					
Adverse drug reactions	SMS/Online		X				
Sexual behaviour	SMS/Online			X	X	X	
Other medications	SMS/Online			X	X	X	
Drug adherence	SMS/Online			X			
Follow up questionnaire	Paper						X
Specimen collection	Number						
Self-collected swabs	3	X					
Self-collected swabs	2						X
Test of cure swab	1						X

*SMS* short message service. 3 swabs collected at recuitment: 1 for whole genome sequencing if required, one for mRNA and 1 for culture. 3 swabs collected at follow up: 1 for whole genome sequencing if required, 1 for mRNA and one for test of cure

### Specimen collection

MSM will be asked to provide self-collected rectal swabs.

#### Specimen processing and extraction

All swabs will be sent to the Molecular Microbiology Laboratory, Royal Women’s Hospital for processing and testing. Swabs collected for routine NAAT and WGS will be rotated in 400 μL phosphate buffered saline for 30 s. Swabs collected for mRNA will be rotated in 1 ml of RNAlater (Lifetechnologies) preservative solution (Ambion, Austin, TX, USA) and stored at -80 °C until further testing is required. An aliquot of 200 μl will be extracted by the automated MagNA Pure 96 isolation and purification system (Roche Diagnostics, Mannheim, Germany) using the DNA and Viral NA Small Volume isolation kit. Following nucleic acid isolation, all samples will be initially assessed for DNA and RNA adequacy with a quantitative PCR for a 260 bp fragment of the human beta-globin gene [39] and 226 bp fragment of U1A transcript. [40] Chlamydia testing will be done by the Cobas 4800 CT/NG assay (Roche Applied Science) as per the manufacturer’s instructions.

#### Genotype (strain) determination

Identification of each chlamydia strain including LGV will be determined by qPCR assays using serovar-specific probes as we have described previously [41].

#### Whole genome sequencing (WGS)

Samples from MSM who test chlamydia NAAT positive at week 4 with the same genotype as their baseline sample will undergo WGS to identify the specific strain for each specimen and identify whether the organisms are identical. We will use a direct DNA probe capture method to capture chlamydial DNA directly from the swab sample and sequence the entire genome [42, 43]. Others have used OmpA genotyping or multi-locus sequence typing to characterise genovar [44], but these techniques are considerably less discriminatory than WGS. Our trial will be the first to use WGS to help differentiate between new infection and treatment failure.

#### mRNA

To ensure only actively transcribed nucleic acid is evaluated (as a marker of active, viable infection), extracted nucleic acid will be treated with 10U/μl DNase (Roche Diagnostic) for 10 min at 37 °C, followed by inactivation of DNase. Resultant RNA will undergo one-step reverse transcription and qPCR using the method by Storm et al. [37]. Any case that has mRNA detected will be classified as a true positive. Cases in which mRNA is not detected will be classified as false positive cases. Our trial will be the first to use mRNA assays to identify false positive cases.

### Data collection (Table 1)

#### Questionnaire at recruitment

Participants will complete a paper-based survey at recruitment covering demographics and sexual health, including symptoms and sexual behaviour data. This will include: number of partners; types of sexual activity (including insertive/receptive anal sex); use of intra-rectal devices (eg sex toys); condom use; type of lubrication used and details about douching pre/post sex and types of fluids used for douching. The questions on douching, water based lubricants and intra-rectal devices have been included because they may reduce the antibiotic concentrations in the rectal mucosa due to epithelial damage [45–48]. HIV status, use of pre-exposure prophylaxis for HIV or anti-retroviral therapy, and most recent viral load will be obtained from their medical record.

#### Weekly data collection

Participants will be asked to respond to a weekly short message service (SMS) that collects (via online link) whether they had: any receptive anal sex in the last week; sex with any new sexual partners; sex without a condom in the last week; used any douching and/or intra-rectal devices; any anogenital symptoms; any chlamydia testing elsewhere; taken any further antibiotics.

#### Side effect reporting

During the first week, participants will also be asked daily via SMS whether they had any diarrhoea or vomiting that could impact on their levels of antibiotic absorption.

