### Intervention

Participants will be randomly allocated to one of the following treatment groups:

Azithromycin: Participants will receive 1 g of active azithromycin (500 mg tablets × 2), plus 13 placebo doxycycline tablets, identical in appearance to the active azithromycin. Participants will be required to take the two azithromycin tablets under observation at time of recruitment and then advised to take a single placebo tablet morning and night for the next 7 days;

Doxycycline: Participants will receive 14 active doxycycline tablets (100 mg), plus one placebo azithromycin tablet, all identical in appearance to active azithromycin. Participants will be required to take one active doxycycline and one placebo azithromycin tablets under observation at time of recruitment and then advised to take a single active doxycycline tablet morning and night for the next 7 days.

Participants will be advised to take the drugs with food to minimize gastrointestinal side effects and to minimize sun exposure or use sun screen to reduce the risk of photosensitivity.

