### Randomization and sequence generation, allocation concealment and blinding

A computer-generated randomization sequence will be created by an independent statistician. Blinded therapy will be prepared by an independent organization and labelled with individual kit numbers according to randomization. Study drugs will be packaged into individually numbered kits stored by independent site pharmacists. All tablets will be identical in appearance and feel, and all medications will be packaged identically to maintain blinding. Participants, physicians, nurses, trial statistician and all other trial staff will be masked to treatment group. The effectiveness of blinding will be tested at completion of the trial when participants will be asked to indicate which treatment they thought they received (including being able to indicate “don’t know”).

The side-effect profiles of the drugs will have negligible impact on blinding. They have been widely used for chlamydia for decades at the dosages we will be using. Their side-effect profiles are well established and similar including minor gastrointestinal upset (nausea, stomach cramps, diarrhoea, vomiting, gastric reflux) [34]. Photosensitivity may occur for doxycycline but is more common with longer or higher dosages [35]. Rash is a rare side effect for each drug, occurring in 0.1–1% of cases [34]. Our packaging will clearly state sunscreen should be used and exposure to sun minimalized, thereby reducing the risk of photosensitivity. We examined the side-effect data from treatment trials for urethral/cervical chlamydia and found that among 17 trials, there was no difference in side-effects (24.0% for azithromycin vs 23.0% for doxycycline, p = 0.45) [36].

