### Adverse events reporting

We do not expect any severe adverse events as these drugs have been widely used for decades and their side-effect profiles are well-established. Nevertheless, we will record adverse events which will be coded using the Medical Dictionary for Regulatory Activities (MedDRA). The percentage of patients with treatment-emergent adverse events will be tabulated by system organ class and severity of these events with particular focus on gastrointestinal events together with severity of these events [49].

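### Table 1 schedules the adverse-reaction SMS only on Days 2-6, which conflicts with the text and stops one to two days before the last tablet

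*Protocol article*

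**What the plan says.** Five places in the protocol article bear on this.

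- **Side effect reporting** gives the frequency and content of the messages: "During the first week, participants will also be asked daily via SMS whether they had any diarrhoea or vomiting". The stated purpose is to pick up symptoms "that could impact on their levels of antibiotic absorption".
- **Follow up, Table 1** has one row for this, "Adverse drug reactions", in SMS/online format. It is marked only under Days 2-6. The cells for Days 1, 7, 14, 21 and 28 are empty.
- **Intervention** sets the tablet calendar. For doxycycline: "Participants will receive 14 active doxycycline tablets (100 mg), plus one placebo azithromycin tablet". One active tablet is taken under observation at recruitment, and men are "then advised to take a single active doxycycline tablet morning and night for the next 7 days". In the azithromycin arm all the active drug is taken under observation on Day 1, followed by 13 placebo tablets on the same calendar.
- **Adverse events reporting** says that adverse events will be recorded and MedDRA coded, with percentages "tabulated by system organ class and severity of these events with particular focus on gastrointestinal events".
- **Secondary analysis** drops from both per-protocol analyses any man who vomits inside an hour of a dose, whichever dose it is.

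**The concern.** Text and table disagree on when men are asked, and on the table's version the asking ends while tablets are still being taken. Two uses of the data depend on it.

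The first is tolerability. The comparison is between a single dose and a seven-day course, and gastrointestinal events are the stated focus of the safety table. A collection period that omits some active dosing days leaves that comparison incomplete.

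The second is the per-protocol population. The vomiting exclusion applies to every dose, so it needs an answer for every dose and a time relative to the dose. Where no message is sent, a man who vomited cannot be identified from this source and stays in the analysis by default.

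Content is a related point. The described message covers two symptoms and no severity. The section on randomization and blinding also names nausea, cramps, reflux and rash, and says: "Photosensitivity may occur for doxycycline but is more common with longer or higher dosages".

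**Working it through.** The protocol states no figure to reproduce here. The check is a count of doses against the queried days.

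**Inputs.** Queried days: 2 to 6 (Table 1). Active doxycycline tablets: 14, of which one is observed on Day 1 (Intervention), leaving 14 − 1 = 13. Active azithromycin: one dose, on Day 1.

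**Day of the last tablet.** Morning and night for seven further days would need 2 × 7 = 14 tablets, but 13 remain. The Intervention section therefore leaves the end of dosing open. Two calendars fit the 14 tablets:

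- A: second tablet on the evening of Day 1. Day 1 has 2 and Days 2-7 have 6 × 2 = 12, total 14; last tablet Day 7.
- B: remaining tablets start on Day 2. Day 1 has 1, Days 2-7 have 12 and Day 8 has 1, total 14; last tablet Day 8.

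Table 1's last message is on Day 6, so collection stops 7 − 6 = 1 or 8 − 6 = 2 days before the last tablet.

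**Recall period.** None is stated, so three assumptions are shown:

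| Assumed recall | Days covered | Doxycycline doses missed, A | Doxycycline doses missed, B | Azithromycin dose day |
|---|---|---|---|---|
| Same day | 2-6 | 2 (Day 1) + 2 (Day 7) = 4 | 1 (Day 1) + 2 (Day 7) + 1 (Day 8) = 4 | missed |
| Previous day | 1-5 | 2 (Day 6) + 2 (Day 7) = 4 | 2 (Day 6) + 2 (Day 7) + 1 (Day 8) = 5 | covered |
| Same day, with the Day 2 message also looking back to Day 1 | 1-6 | 2 (Day 7) = 2 | 2 (Day 7) + 1 (Day 8) = 3 | covered |

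The range is 2/14 = 14% to 5/14 = 36% of active doxycycline doses.

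**If the text were followed instead.** Same-day messages on Days 1-7 would cover 14 of 14 doses on calendar A and 13 of 14 on calendar B, plus the azithromycin dose day.

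**Vomiting rule.** Men in both arms have 14 tablet-taking occasions (one observed, then 13), so the same 2 to 5 of 14 occasions lack a described vomiting query in either arm. The message as described also records no time relative to dose, even on the days covered.

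**Other sources.** The weekly SMS, as listed, asks about anogenital symptoms and further antibiotics, but not about drug reactions. The week-4 questionnaire asks about symptoms without listing them, about three weeks after dosing. The adherence questionnaire at the end of week 1 is not described as asking about vomiting.

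**The case against.** The strongest reply has three parts.

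**Other capture.** The daily SMS has its own purpose, antibiotic absorption, and need not be the trial's adverse-event instrument. The section on adverse events provides for recording and coding without naming the SMS as the source. The abstract mentions questionnaires on adverse drug reactions in general, and the week-4 questionnaire covers symptoms. Forms and grading are commonly left to the full protocol. This stands. A reader might infer that the planned table cannot be produced, or that skin and other organ classes would be close to zero by construction. The article does not show that. It shows only that this SMS, on its own, could not supply organ classes and severity.

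**No demonstrated bias.** A reader might infer that the window favours one arm. Both blinded arms share one tablet calendar and one message schedule, and every message in Table 1 follows the whole azithromycin dose. With same-day recall the azithromycin dose day is lost; with previous-day recall only doxycycline loses active doses. No recall period and no data on when reactions begin are given, so the direction of any distortion cannot be derived. This also stands. What survives is that the coverage of active doses is incomplete and differs between arms by an amount that depends on unstated details.

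**Low stakes.** Adverse events are neither a primary nor a secondary outcome. That limits the weight of the point, but the vomiting exclusion defines the population for two efficacy analyses, so the data are not only descriptive.

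None of this removes the conflict between Table 1 and the text.

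**Conclusion.** The point holds as a conflict between passages and a gap in collection. On Table 1's schedule, adverse-reaction messages end one to two days before the last tablet, and 2 to 5 of 14 active doxycycline doses go unqueried; with same-day recall the azithromycin dose day is unqueried as well. The range rests on the three recall assumptions and two tablet calendars shown, because the article fixes neither. It counts doses, not events: how many reactions or vomiting episodes would be lost, and in which arm, cannot be estimated from the article.

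The firmer consequence is for the per-protocol analyses, whose vomiting exclusion cannot be applied to every dose from the SMS as described. Severity is minor to moderate, since the week-4 NAAT outcome and the modified intention-to-treat analysis do not depend on these data.

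**What to change.** Reconcile Table 1 with the sections Side effect reporting and Intervention, including the tablet count that leaves the last dosing day open. Then:

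- Run the daily SMS in both arms from Day 1 through the day after the last scheduled tablet, whichever day that proves to be.
- State a 24-hour recall period in the message.
- Where vomiting is reported, ask when it occurred relative to the dose, so that the one-hour exclusion can be applied.
- Optionally, add to the existing online link the other reactions that the protocol names (nausea, stomach cramps, reflux, rash, photosensitivity).

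At one message per day, Table 1 implies five messages. The change makes eight (Days 1-8, last tablet Day 7) or nine (Days 1-9, last tablet Day 8), so three or four more per man. The Day 7 question can go with the SMS already scheduled that day. The cost is a few automated messages, a one-line change to Table 1 and slightly more response burden, with no extra visit.

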#### At the 4-week follow up

Participants will complete another paper-based questionnaire that collects information regarding symptoms and sexual behaviour data, diagnosis of any STIs during follow up (which will be validated against their medical record) and what treatment they believe they received. We will also collect information about any recent HIV viral loads and/or CD4 counts.

### Drug adherence monitoring

Participants will be asked to complete a questionnaire about drug adherence at the end of week 1. They will also be asked to return the pill bottle for a pill count as proxy measure of drug adherence. A previous study comparing self-report with measured adherence using the Medication Event Monitoring System, found 83% concordance between self-report and measured adherence for taking 11–14 doses among 206 men and women [28].

### Adverse events reporting

We do not expect any severe adverse events as these drugs have been widely used for decades and their side-effect profiles are well-established. Nevertheless, we will record adverse events which will be coded using the Medical Dictionary for Regulatory Activities (MedDRA). The percentage of patients with treatment-emergent adverse events will be tabulated by system organ class and severity of these events with particular focus on gastrointestinal events together with severity of these events [49].

### Sample size

Our hypothesis is that azithromycin efficacy will be less than that of doxycycline. On the basis of our meta-analysis, we assume that the microbial cure among the doxycycline arm at 4 weeks will be 98% compared to azithromycin at 93%. We will recruit 700 men in total (350 in each group) which, allowing for a very conservative 14% loss to follow up (based on our experience with similar trials of MSM) [50] and a further loss of 6% due to a LGV diagnosis at the end of the trial, will give us an effective sample size of 560. This sample size will allow us to detect a 5% difference between doxycycline and azithromycin microbial cure at 4 weeks with 80% power and a 6% difference with 90% power. If microbial cure is 96% among those treated with doxycycline at week 4, then we will have 80% power to detect a 6% difference and 90% power to detect a 7% difference (Table 2).

**Table 2 Tab2:** Sample size calculation

Doxycycline cure	98% cure		96% cure	
Power	80%	90%	80%	90%
Difference to detect^a^				
%	538	720	762	1018
6%	412	552	560	756
7%	332	442	444	592

^a^Assumes azithromycin microbial cure will be 5–7% lower. Sample size calculation assumes 5% significance

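### At 96% doxycycline cure, the stated 90% power for a 7-point difference does not match Table 2, which needs 592 evaluable men against 560 available

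*Protocol article*

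**What the plan says.** All of this is in the Sample size section of the protocol article.

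- Recruitment is 700 men, 350 per group. After 14% loss to follow-up and a further 6% excluded for LGV, the plan "will give us an effective sample size of 560".
- The main assumption is 98% cure on doxycycline against 93% on azithromycin. The text claims 80% power for a 5-point and 90% power for a 6-point difference.
- A fallback takes doxycycline cure to be 96% instead. For that case the article says: "then we will have 80% power to detect a 6% difference and 90% power to detect a 7% difference". The sentence cites Table 2 as its source.
- Table 2 gives total sample sizes by doxycycline cure (98% or 96%), difference (5, 6 or 7 points) and power (80% or 90%). Its 7-point row reads 332 and 442 at 98% cure, then 444 and 592 at 96% cure. Its footnote adds: "Sample size calculation assumes 5% significance".

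**The concern.** A power statement that cites a table should agree with it. Here the text grants 90% power to 560 men in a scenario where the table asks for 592, which is 32 more (592/560 = 1.057, so the table figure is 5.7% above what is available). Anyone who checks the sentence against its own source finds that it fails.

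The 96% case is the only alternative cure rate for which the article states power, so it is the statement a reader would turn to if cure on doxycycline came out below the planning value. What is at stake is the accuracy of that one statement. Recruitment, the analysis and power in the main scenario do not depend on it.

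**Working it through.** **Inputs.** Cure rates, differences, power levels, the 5% significance level, the 560 evaluable men and the Table 2 cells come from the Sample size section. The chi-square test comes from the Analysis section. The article does not say whether the 5% is two-sided or which formula was used; both are inferred below from the table.

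**Step 1: the effective sample.** 700 × (1 − 0.14 − 0.06) = 700 × 0.80 = 560, or 280 per arm. This matches the text.

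**Step 2: the formula behind Table 2.** For 1:1 allocation, two-sided 5%, pooled variance under the null and no continuity correction, with p̄ the mean of p₁ and p₂:

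n per arm = [1.96·√(2p̄(1−p̄)) + z_β·√(p₁(1−p₁) + p₂(1−p₂))]² / (p₁−p₂)²

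Rounded up per arm and doubled:

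| Difference | 98%, 80% power | 98%, 90% power | 96%, 80% power | 96%, 90% power |
|---|---|---|---|---|
| 5 points | 538 | 720 | 762 | 1018 |
| 6 points | 412 | 552 | **566** (printed 560) | 756 |
| 7 points | 332 | 442 | 444 | 592 |

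Eleven of the twelve printed cells are reproduced exactly, including 592. One-sided, unpooled and continuity-corrected versions do not reproduce the table.

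**Step 3: the 592 cell in full.** p₁ = 0.96, p₂ = 0.89, p̄ = 0.925.

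- √(2 × 0.925 × 0.075) = √0.13875 = 0.3725
- √(0.0384 + 0.0979) = √0.1363 = 0.3692
- n = (1.960 × 0.3725 + 1.2816 × 0.3692)² / 0.0049 = (0.7301 + 0.4731)² / 0.0049 = 295.4, so 296 per arm and 592 in total

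**Step 4: power with 280 per arm, 96% versus 89%.**

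z = (0.07 × √280 − 0.7301) / 0.3692 = (1.1713 − 0.7301) / 0.3692 = 1.195, so power = 88.4%.

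Solving the same equation for the difference that has 90% power at 280 per arm gives about 7.24 points.

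**Step 5: the four power statements against the printed table.**

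| Statement | Table 2 cell | Met by 560? |
|---|---|---|
| 98%, 5 points, 80% | 538 | yes |
| 98%, 6 points, 90% | 552 | yes |
| 96%, 6 points, 80% | 560 | yes |
| 96%, 7 points, 90% | 592 | **no** |

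**Step 6: the 6-point cell.** For 96% versus 90%, √0.1302 = 0.3608 and √0.1284 = 0.3583. Then n = (1.960 × 0.3608 + 0.8416 × 0.3583)² / 0.0036 = 282.7, so 283 per arm and 566 in total. The unpooled formula gives 560 here, but it matches no other cell. Pooled power at 280 per arm is 79.6%.

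**Step 7: sensitivity to method, 96% versus 89%.**

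| Method | Total N for 90% power | Power at 280 per arm |
|---|---|---|
| Pooled (Table 2 formula) | 592 | 88.4% |
| Unpooled | 586 | 88.7% |
| Continuity-corrected | 648 | 84.9% |
| Exact enumeration, uncorrected chi-square | not computed | 89.9% |
| One-sided 5%, pooled | 482 | 93.5% |

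None of the two-sided formulas brings the required total down to 560. A one-sided test would, but it does not reproduce Table 2.

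**The case against.** **The planned test performs better than its approximation.** The Analysis section specifies a chi-square test, and exact enumeration of the uncorrected test at 280 per arm gives 89.9% power for 96% versus 89%. On that basis the stated 90% is right to the nearest point. This stands as to practical size. It does not remove the inconsistency, because the article rests its claim on Table 2 and names no exact calculation.

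**The losses might be applied in sequence.** The 6% is described as a further loss, and 700 × 0.86 × 0.94 = 566. At 283 per arm, power for 96% versus 89% is 88.7% pooled and 90.2% exact. But the article prints 560, and 566 is still below 592.

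**Readings that go too far.**

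- A reader might infer that both statements for 96% cure fail. They do not. The printed cell for 6 points and 80% power is 560 and agrees with the text. Even with the recomputed 566, power is 79.6% pooled and 81.3% exact, so 80% holds to rounding.
- A reader might infer that the trial is underpowered. At 280 per arm, the main scenario of 98% versus 93% has 81.6% power by the Table 2 formula, and both statements at 98% cure agree with the table.
- A reader might treat 96% as the likelier cure rate, since reinfections count against cure in the primary outcome. The article plans on 98% and offers 96% only as an alternative. It gives no figures for ranking the two.

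**Conclusion.** The point holds as a modest inconsistency between text and table. One of the four power statements, 90% power for 7 points at 96% doxycycline cure, is contradicted by the table cited for it: 592 required against 560 available. By the table's own formula the power is 88.4%, an overstatement of 1.6 points, and 90% power is reached at about 7.24 points. By exact enumeration the overstatement is about 0.1 point.

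This rests on 280 evaluable men per arm, a two-sided 5% level and the pooled-variance formula. The last two are inferred from the 11 matching cells. The mismatch of 592 with 560 needs none of these inferences, since both figures are printed.

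The 6-point cell at 96% cure and 80% power is a secondary matter: it is the only cell that departs from the formula (560 printed, 566 computed), and the 80% statement survives either way.

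**What to change.** Restate the fallback sentence in one of two ways:

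- By the Table 2 formula: *with 560 evaluable men and 96% cure on doxycycline, power is about 80% for a 6-point difference and about 88% for a 7-point difference.*
- By exact calculation: give about 81% for 6 points and about 90% for 7 points, name the method (exact power of the uncorrected chi-square test), and do not cite Table 2 as the source.

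Check the Table 2 cell for 96% cure, 6 points and 80% power. If the pooled formula was intended throughout, it becomes 566, and the word *about* before 80% covers the 6-man gap to 560.

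The cost is one sentence and possibly one table cell. Enrolment stays at 700. Reaching 592 evaluable men under the article's 20% total loss would take 592 / 0.80 = 740 recruits, and a gap this small in a fallback scenario does not call for that.
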